## Abstract

**Background:**

Diabetic peripheral sensory neuropathy (DPSN) presents with pain or neuropathy symptoms and disturbances in lower limb sensory functions, leading to complicated diabetic foot conditions and declining quality of life. There is a research gap on the non-pharmacological conservative approach to this disabling condition. The objective of this study is to evaluate the effectiveness of the neurodynamic approach, along with electrophysical stimulation, in reducing the severity of neuropathic symptoms and improving the quality of life in patients with DPSN.

**Methods:**

An assessor and patient-blinded randomized clinical trial (RCT) on 90 DPSN cases through hospital-based simple random sampling. Participants will be randomly assigned equally to either the Neurodynamic approach or the Sham neurodynamic approach group by concealed allocation between April and August 2025 at the Nurul Islam Diabetic Center in Jashore, Bangladesh. The experimental group will receive the Neurodynamic approach, and the control group will receive the sham approach; however, both groups will receive transcutaneous electrical nerve stimulation (TENS) and home exercises for 12 sessions over 4 weeks. A pretest will be taken at baseline, a posttest after 4 weeks, and a follow-up evaluation after 12 weeks. In addition to outcome measures, manageable and fatal adverse events will be documented and reported.

**Discussion:**

This trial will be implemented in the non-pharmacological management of prevalent cases with DPSN and diabetic foot, sparing the burden of polypharmacy in people living with diabetes. Moreover, a positive result may guide clinicians toward an alternative in evidence-based practice, especially in a low-resource country like Bangladesh. This single-center trial may be limited by a lack of external generalizability, but it will lead to multicenter, large-sample studies in the future.

**Trial registration:**

Registered from Clinical Trial Registry of India CTRI/2025/01/079801 [Registered on: 30/01/2025] Trial Registered Prospectively.

## Introduction

Diabetes mellitus (DM) is a chronic condition resulting from insufficient insulin in the body or reduced insulin effectiveness, leading to high blood sugar levels [1]. Diabetes is classified into two main types: type-1 diabetes, where the body does not produce insulin and requires external insulin for survival, and type-2 diabetes, where the body becomes resistant to insulin. Type-2 diabetes is the most common, affecting around 90–94% of people with diabetes worldwide [2]. The prevalence of diabetes continues to rise, with an estimated 422 million people affected worldwide, especially in low- and middle-income countries [3]. One of the most serious complications of diabetes is diabetic peripheral neuropathy (DPN), a condition that occurs when high blood sugar damages the nerves, particularly in the legs and feet [4]. Nearly 50% of people with diabetes develop DPN, making it one of the leading causes of chronic pain, numbness, and mobility problems. Symptoms of DPN include tingling, burning pain, numbness, and reduced sensation, especially in the lower limbs [5]. Diabetic neuropathy is usually classified into two main categories: autonomic neuropathy and sensory neuropathy. The condition (DPN) presents as sensory, motor, and autonomic dysfunction, leading to symptoms such as pain, weakness, tingling, and numbness [6]. Diabetic peripheral sensory neuropathy (DPSN) is characterized by distal symmetric neuropathy that involves numbness, discomfort, loss of sensation, and abnormal sensation [7]. Affected individuals of DPSN often experience altered sensations, including electric shock-like pain, reduced heat and touch sensitivity, and progressive loss of protective sensation [8]. These issues not only affect daily life but also increase the risk of serious complications like foot ulcers, infections, and amputations. Remarkably, DPSN is responsible for 80% of diabetes-related foot ulcers, which can lead to severe infections and a high risk of death [9,10].

DPSN is a common problem in both type-1 and type-2 diabetes, but research shows that it develops differently in each condition. The differences in metabolism between T1DM and T2DM lead to different types of nerve damage [11]. It develops from a combination of metabolic and blood vessel-related problems that impair nerve function [12]. Prolonged high blood sugar levels lead to oxidative stress, inflammation, and reduced blood supply, which harm nerve fibers [13]. Over time, these changes cause loss of protective nerve coverings (demyelination) and nerve degeneration, leading to sensory and motor dysfunction [14]. One of the major biomechanical effects of DPSN is reduced nerve mobility and flexibility, which affects nerve gliding through tissues [15]. Research has shown that people with DPSN exhibit reduced nerve mobility and stiffness in the lower limbs, particularly during movements such as ankle dorsiflexion and hip flexion [16]. This reduced nerve flexibility contributes to increased pain, muscle weakness, and difficulty with movement, making walking and daily activities challenging [17]. As a result, individuals with DPSN are at a higher risk of falls, injuries, and disability [18]. The biomechanical changes resulting from DPSN may translate to increased plantar pressures in the foot, which contribute to the pathogenesis and development of foot ulcers, especially in the forefoot [19]. In particular, the first metatarsophalangeal joint has been implicated as a site of biomechanical dysfunction leading to elevated plantar pressures during gait, promoting ulceration at this site [20,21].

Both pharmaceutical (medications) and non-pharmacological (non-medication) treatments are used to manage DPSN [22]. Antidepressants, anticonvulsants, and gabapentinoids are examples of painkillers that can help decrease symptoms, though they do not totally treat DSPN and frequently have negative side effects [23]. In recent years, physiotherapy-based treatments have gained attention as an alternative approach to managing DPSN. Neurodynamic mobilization is one of these that has to improve nerve function and reduce pain [24,25]. Specific nerve movements are used in neurodynamic mobilization to increase blood flow to the affected areas, decrease stiffness, and improve the nerve’s capacity to glide smoothly [26]. According to studies, neurodynamic exercises can help people with mild-to-severe DPSN move more freely, reduce pain, and improve lower-limb flexibility [27].

There is still limited research on the effectiveness of neurodynamic mobilization for DPSN in Bangladesh. Most studies have been conducted in animals or have focused on a single nerve, making it difficult to draw strong conclusions for human patients [28]. This study aims to fill this research gap by evaluating the effects of neurodynamic mobilization combined with foot exercises on neuropathy severity, pain, sensory disturbances, and quality of life in people with DPSN. The study is based on the hypothesis that neurodynamic mobilization will significantly improve nerve function, reduce pain, and enhance the quality of life (QoL) compared to standard treatments. The objectives of the study are (1) to find out the outcome of the neurodynamic approach on the severity of neuropathy, (2) to elicit the effectiveness of the neurodynamic approach in reducing neuropathic pain, and (3) to evaluate the impact of the neurodynamic approach on quality of life in individuals with lower limb DPSN.

## Methods

### Study design

The study will be an assessor and patient-blinded Randomized Clinical Trial (RCT) at the Nurul Islam Diabetic Center in Jashore, Bangladesh. Ninety (90) patients diagnosed with DPSN by a diabetic foot surgeon and experiencing pain, burning, or tingling in the lower limbs or peripheral nerves will be randomly recruited via hospital-based simple randomization between April 2025 and August 2025. The recruited patients will be randomly allocated to either the Neurodynamic Mobilization (Experimental) (n = 45) or Sham Neurodynamic Mobilization (Control) (n = 45) groups in a 1:1 ratio using simple random sampling. The experimental group will receive Neurodynamic mobilization, and the control group will receive Sham Neurodynamic Mobilization for 12 sessions in 4 weeks; both groups will receive common foot exercises and transcutaneous electrical nerve stimulation (TENS) as a common treatment. The post-test will be taken 4 weeks after baseline assessment and recruitment, and the follow-up will be taken 12 weeks after the post-test. The follow-up assessment of the last recruited participant will end by August 2025. The study protocol will follow the Fig 1. SPIRIT (Standard Protocol Items: Recommendations for Interventional Trials) guideline of the study protocol, ensuring a clear and comprehensive study design, including participant recruitment, randomization, intervention allocation, and follow-up assessments.. The results will be reported in accordance with the CONSORT (Consolidated Standards of Reporting Trials) flow diagram (Fig 2) of participant progression, which shows the flow of participants through the enrollment, allocation, follow-up, and analysis phases of the randomized clinical trial.

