### Sample size calculation

The number of patients was determined using G*Power (version 3.1.9.7) based on changes in neuropathic pain scores from a study by [29], which examined the effect of the Michigan Diabetic Neuropathy Score (MDNS), a validated tool used to assess the severity of diabetic peripheral neuropathy. 42 subjects per group were shown to be necessary based on an effect size of 0.62, an alpha level of 0.05, and a power of 0.8. Hence, the total sample size was 84. [30]. We anticipate a 10% dropout rate, so we will recruit 90 participants in total and allocate them equally between the two groups.

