### Inclusion

Adults between 40 and 70 years old [24].Who have been diagnosed with Type-2 DPSN & Type-1 DPSN [31]Individuals who will give informed consent.The Michigan Diabetic Neuropathy Score (MDNS) is more than 6 [32].Symmetrical or asymmetric peripheral neuropathy accompanied by lower extremities discomfort lasting more than six months [32].

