### Secondary outcomes

**1. 10 cm Visual Analog Scale (VAS):**
The Visual Analog Scale (VAS) is a widely used tool for measuring pain and is known for its high accuracy (ICC = 0.98). Participants will be asked to place a mark on a straight line to show how much pain they are feeling at that moment. The pain level is then measured in millimeters to quantify pain level [51–54].

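### Entry does not require pain and the planned VAS comparison has no baseline covariate, so the secondary pain effect may be diluted by participants who start at or near 0

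*Protocol article*

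**What the plan says.** All references are to the protocol article.

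- **Entry.** Study design admits patients "experiencing pain, burning, or tingling in the lower limbs or peripheral nerves". The Inclusion list asks for "Symmetrical or asymmetric peripheral neuropathy accompanied by lower extremities discomfort lasting more than six months" and that "The Michigan Diabetic Neuropathy Score (MDNS) is more than 6". Neither the Inclusion nor the Exclusion list sets a minimum VAS or requires current pain.
- **Objective.** The second objective in the Introduction is "to elicit the effectiveness of the neurodynamic approach in reducing neuropathic pain".
- **Measure.** Pain is a secondary outcome on a 10 cm VAS. Participants "place a mark on a straight line to show how much pain they are feeling at that moment".
- **Analysis.** Data analysis specifies a repeated-measures ANOVA with group, time and their interaction, on an intention-to-treat basis for every randomised participant. It names no covariate and no analysis by baseline pain.
- **Sample size.** The calculation is described as "based on changes in neuropathic pain scores" from a cited study, but the same sentence attributes that study's result to MDNS. It uses an effect size of 0.62, alpha 0.05 and power 0.8, giving 42 per group.

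**The concern.** The alternatives at entry are joined by an *or*, so tingling alone qualifies. Discomfort need not mean pain either: the Introduction lists it beside numbness and loss of sensation as features of DPSN. The one scored threshold does not select for pain, because the Primary outcomes section describes MDNS as vibration, light-touch and pinprick testing, on which a numb and painless foot can score high.

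A participant who enters with a VAS of 0 can only stay there or get worse, whichever arm is assigned. Someone just above 0 has little room to improve. Rating pain only at the moment of assessment makes low baseline scores more likely, but the floor for patients who truly have no pain would remain under any recall period.

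Two things follow. The mean VAS difference is pulled towards zero, and the mixture of people who can and cannot improve adds variance that the planned model does not remove. A null VAS result could then reflect who was enrolled and would not show that the technique fails to reduce neuropathic pain.

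**Working it through.** **Inputs from the article:** d = 0.62, alpha 0.05, 42 per group (Sample size calculation).

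**Assumptions, because the article gives no figures:** the pain-free share f (10%, 20%, 30%); that 0.62 applies to VAS change in participants with pain, with SD 1; that pain-free participants show no change in either arm; a control-arm mean improvement m among those with pain of 0, 0.5 or 1.0 SD.

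**1. The plan's own figure.** A two-sided two-sample t-test with d = 0.62 and 42 per group has power 0.802 (41 per group gives 0.792). The stated 42 reproduces; one-sided testing would need only 33 (normal approximation).

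**2. Dilution without baseline adjustment.**

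- Mean difference = (1 − f) × 0.62.
- Variance in an arm whose painful participants improve by μ on average = (1 − f) + f(1 − f)μ², with μ = m in control and m + 0.62 in the active arm.
- d = mean difference ÷ square root of the average of the two variances.

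Example, f = 0.2 and m = 1.0: the difference is 0.8 × 0.62 = 0.496. The variances are 0.8 + 0.16 × 1.00 = 0.960 and 0.8 + 0.16 × 1.62² = 1.220, averaging 1.090. So d = 0.496 ÷ 1.044 = 0.475, and power is 0.576.

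| f | d (m = 0 / 0.5 / 1.0) | Power (m = 0 / 0.5 / 1.0) |
|---|---|---|
| 10% | 0.583 / 0.567 / 0.541 | 0.751 / 0.729 / 0.688 |
| 20% | 0.544 / 0.517 / 0.475 | 0.693 / 0.649 / 0.576 |
| 30% | 0.504 / 0.469 / 0.418 | 0.627 / 0.564 / 0.473 |

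Leaving the SD at 1 gives power 0.715, 0.613 and 0.502, inside these ranges. The Discussion expects the control group to improve through exercises and TENS, so m above 0 is the more relevant case.

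**3. All participants, adjusted for baseline pain.** Adjusting for whether pain is present at baseline removes the part of the variance that depends on m. What remains is (1 − f) + f(1 − f) × 0.31², where 0.31 is half of 0.62. At f = 0.2 this is 0.8 + 0.16 × 0.0961 = 0.815, so d = 0.496 ÷ 0.903 = 0.549.

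**4. Only participants with pain,** 42(1 − f) per arm at d = 0.62.

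| f | Power, all adjusted | Power, painful only |
|---|---|---|
| 10% | 0.755 | 0.758 |
| 20% | 0.701 | 0.707 |
| 30% | 0.639 | 0.647 |

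Adjustment gives almost the same power as exclusion and drops nobody. Step 3 uses a yes/no indicator of pain; baseline VAS as a linear covariate only approximates it. Adjustment does not change the estimate itself, which remains (1 − f) × 0.62; only the analysis in step 4 estimates 0.62.

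**5. A higher cut-off.** Suppose 20% are pain-free and a further 20% have pain below some cut-off, such as 30 mm. Then 42 × 0.6 = 25.2 per arm remain, and power is 0.58. That is below the 0.65 of the unadjusted analysis of everyone (f = 0.2, m = 0.5).

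**The case against.** **The average over all participants is a legitimate target.** The trial concerns people with DPSN, not only painful DPSN, and the mean over all randomised is a valid estimate for that population. This stands. It rules out calling the planned comparison biased, and it rules out replacing the analysis population. It does not make a null result interpretable against an objective worded as reducing neuropathic pain.

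**The outcome is secondary.** This stands. Entry requires MDNS above 6, so the primary outcome has no such floor.

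**The size is unknown.** This also stands. The pain-free share is not given, and if nearly everyone enrolled has pain, the loss is small. The assumption of no change in either arm is a simplification too: a score of 0 can rise, and the safety section lists a temporary increase in pain as a possible adverse event.

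**Covariates and supplementary subsets often belong in the SAP, which is not shown.** In part. A SAP may already deal with this, but the article fixes the model and the analysis population without either element.

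A reader might go further in two ways that the document does not support. One is that the sample size presupposes pain that can change. The sentence in question names pain scores and MDNS together, and no VAS effect size or VAS power is claimed anywhere. The other is that pain-free participants should be barred at entry, or that the pain objective should be analysed only above a cut-off such as 30 mm. Such a cut-off on one momentary rating would also remove people who can improve, including those with intermittent pain who are comfortable at that visit, and it can cost more power than the dilution it is meant to cure.

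**Conclusion.** The point holds as a limited one. The entry rule allows participants with no pain, and the planned VAS analysis includes them without adjusting for where they started. Under the stated assumptions, power for the pain outcome is about 0.69–0.75, 0.58–0.69 or 0.47–0.63 at 10%, 20% or 30% pain-free, against 0.80 if everyone has pain. These figures illustrate the mechanism. They do not predict this trial's power, because both the pain-free share and the use of 0.62 for VAS are assumed. The consequence is a smaller average effect, lower power and an ambiguous null result for one secondary outcome. MDNS is untouched, and the error rate for false positives is not raised.

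**What to change.** In Data analysis, for the VAS:

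1. Keep all randomised participants, and analyse follow-up VAS by ANCOVA or a mixed model with baseline VAS as covariate.
2. Report by arm the number of participants with a baseline VAS of 0.
3. Prespecify one supplementary analysis, by randomised arm, of participants with a baseline VAS above 0. Randomisation procedures places allocation after the baseline assessment, so this subset is fixed before assignment and the randomised comparison is kept.

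The entry criteria stay as they are, and no pain cut-off defines the main analysis population.

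The cost is a few sentences and no new data, since baseline VAS is already collected. The downside is one extra secondary analysis in fewer participants, which should be labelled as supplementary.

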Despite these promising findings, this study will have some limitations**.** The sample size may be relatively small, and the study will be conducted at a single center, which may limit the generalizability of the results. Additionally, the long-term effects of neurodynamic mobilization were not assessed beyond the 12-week follow-up period. Future studies should include larger sample sizes, multiple study centers, and longer follow-up periods to determine whether the benefits of neurodynamic mobilization are sustained over time [52–54,57,58].

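### Recruitment and the last participant's follow-up are both dated to August 2025, although each participant needs 16 weeks

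*Protocol article*

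**What the plan says.** Four statements in the protocol article's Study design section set the calendar:

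- Recruitment: patients "will be randomly recruited via hospital-based simple randomization between April 2025 and August 2025".
- Post-test: "The post-test will be taken 4 weeks after baseline assessment and recruitment".
- Follow-up: "the follow-up will be taken 12 weeks after the post-test".
- End of the trial: "The follow-up assessment of the last recruited participant will end by August 2025".

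The Methods part of the abstract ties the same months to random assignment, which takes place "by concealed allocation between April and August 2025 at the Nurul Islam Diabetic Center". It gives the visits as follows: "A pretest will be taken at baseline, a posttest after 4 weeks, and a follow-up evaluation after 12 weeks". The limitations paragraph of the Discussion says that long-term effects "were not assessed beyond the 12-week follow-up period". Neither the abstract nor the Discussion says from which date the 12 weeks run.

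The Data analysis section specifies an intention-to-treat analysis of all randomised participants, a repeated-measures ANOVA with a group-by-time term, and last observation carried forward for missing data.

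**The concern.** Someone recruited in August 2025 cannot complete a 16-week course in August 2025, so the recruitment window and the end date exclude each other. One of them must give way, and the article does not say which.

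The choice affects the data. If enrolment follows the stated window and data collection keeps to the stated end date, later recruits have no follow-up score and the latest have no post-test score. Under the carry-forward rule, week-4 or baseline values would stand in for the missing ones. The last time point in the group-by-time analysis would then largely repeat earlier measurements and say little about whether any effect persists.

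A smaller matter is the abstract. It lists the follow-up in parallel with a post-test that is counted from baseline, so a reader who sees only the abstract may take the follow-up to be at week 12.

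**Working it through.** The documents give no computed figure for the calendar, so there is none to reproduce. The check is date arithmetic.

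**Inputs**

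- Recruitment and assignment: April to August 2025 (Study design; abstract). Exact days are not given. I take 1 April to 31 August, counted inclusively: 30 + 31 + 30 + 31 + 31 = 153 days.
- End of last follow-up: by August 2025 (Study design). I take 31 August, the most generous reading.
- Time per participant: 4 + 12 = 16 weeks = 112 days (Study design).
- Participants: 90 (Sample size calculation).

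**Step 1. Keep the end date and find the last possible enrolment.**
31 August − 112 days = 11 May 2025. The enrolment window is 1 April to 11 May: 30 + 11 = 41 days. The required rate is 90 ÷ (41 ÷ 7) = 15.4 patients per week.

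**Step 2. Keep the recruitment window and find the last follow-up.**
31 August + 112 days = 21 December 2025. If the last patient enrols as early as 1 August, the last follow-up is still 21 November 2025.

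**Step 3. Does reading the abstract as week 12 remove the conflict?**
31 August − 84 days = 8 June 2025, and 31 August + 84 days = 23 November 2025. The conflict remains.

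**Step 4. What would be missing if both dates were enforced?**
Two assumptions are added here: even enrolment from 1 April to 31 August, and data collection stopping on 31 August.

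| Enrolled | Days | Share of 153 | Of 90 | Data reached by 31 August |
|---|---|---|---|---|
| 1 April to 11 May | 41 | 27% | about 24 | Week 16 |
| 12 May to 3 August | 84 | 55% | about 49 | Week 4 only |
| 4 to 31 August | 28 | 18% | about 16 or 17 | Baseline only |

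The second group would have week-4 scores carried to week 16, and the third would have baseline scores carried to both later visits.

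**Step 5. How sensitive is this to the dates chosen?**
If enrolment ended on 1 August (123 days) and data collection on 31 August, 41 ÷ 123 = 33% could reach week 16, so 67% could not, while everyone could reach week 4. On a week-12 reading, 69 ÷ 123 = 56% could reach the visit and 44% could not.

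**The case against.** The best defence is that April to August 2025 was meant as the period of the whole study. The sentence about the last recruit's follow-up commits the team to completing it, and loose wording is at least as plausible as a plan to enrol people who cannot be followed. On that reading the schedule works if enrolment closes by about 11 May. The documents give no recruitment rate, so 15 patients a week can be called neither feasible nor infeasible. This is a fair account of what may have been intended, but the text does not say it: both places attach the months to recruitment or assignment, and no earlier closing date appears. The dates still need correcting.

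Three stronger readings are tempting, and the documents do not support them.

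- A reader might infer that the follow-up is defined as both week 12 and week 16. Only the Study design section anchors it, and that gives week 16. The abstract and the Discussion are unanchored and could be shorthand for 12 weeks after the post-test. They are ambiguous, not a rival definition. The SPIRIT schedule figure, not shown here, may state the timing.
- A reader might infer that most follow-ups will be missing. That requires late enrolment, an even rate and a hard stop on 31 August. The article states no accrual pattern and no data closure date, and a slipped calendar could simply delay the finish.
- A reader might infer that the primary assessment itself is lost for late recruits. The Michigan score is named as the primary outcome without a primary time point, so week 4 cannot be called primary.

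The lack of a visit window is no fault either, since an article may leave that to the full protocol.

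**Conclusion.** The contradiction in the dates stands. It rests only on the stated months and the stated 16 weeks, and it survives the most generous reading of the end date. As written, the schedule cannot be followed: the two dates are short of compatibility by up to 16 weeks if enrolment runs to the end of August.

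The size of any data loss is conditional. With even enrolment to 31 August and a cut-off that day, about 73% would lack a week-16 score and about 18% a week-4 score. These figures describe what enforcing both dates would do and are not a forecast. The unanchored 12 weeks in the abstract is a secondary point of clarity.

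**What to change.** State one recruitment closing date and one last-follow-up date that are at least 16 weeks apart, by one of two routes:

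- close enrolment by about 11 May 2025 and keep the August finish; or
- keep enrolment open to 31 August 2025 and move the last follow-up to about 21 December 2025.

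In either case, say that the data will be closed only after the last participant's follow-up is due, so that the carry-forward rule is not used for visits that the calendar cut off. In the abstract, add the anchor already given in Methods: 12 weeks after the post-test, which is week 16 from baseline. The definition in Methods can stay as it is.

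No extra patients are needed. The first route costs enrolment time, with about 15 patients a week to be found at one centre. The second costs a finish nearly four months later.
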